### Randomisation

Before the beginning of the implementation phase, clusters were randomly allocated a time when they are to be given the intervention. In agreement with the CONSORT statement extended to cluster randomised trials, the team of statisticians, which was blinded to the identity of the clusters, randomised the clusters using computer generated random numbers [21]. The randomisation sequence was therefore established before the beginning of program implementation. Only the research team was aware of the allocation of all of the clusters. In order to maintain allocation concealment, GPs will be informed of their allocation time only in the month prior to the date of implementation in their cluster. This one-month delay is necessary for the organisation of their training for the InPAct program.

It is impossible to blind patients and GP participants for the intervention, due to the nature of the intervention, *i.e.*, training GPs in the distribution of a booklet to patients. Outcome assessment will, however, be essentially blinded. Indeed, most of the data are collected in a blinded fashion by clinical research associates, whereas the only non-blinded medical data will be those collected by the GPs.

### Statistical analysis

The quantitative characteristics of the patients included during the control and intervention periods will be described either by using the mean and the standard deviation, or by using the quartiles and the minimum and maximum values, depending on the shape of the distribution. The qualitative characteristics of the patients will be described using the absolute and relative frequencies in the different categories. The comparisons between the two groups will be carried out using a student-*t* test or a non-parametric test for the quantitative characteristics and a chi-squared test or a Fisher’s exact test for the qualitative characteristics.

A stepped wedge design is a unidirectional crossover trial. The particularity of this design, in comparison with traditional crossover studies, is that the information allowing quantification and testing of the intervention effect is present within and between the clusters. As recommended by Hussey and Hughes [20], the analysis of the intervention effect on the main outcome will be carried out using a mixed logistic model with a random intercept, in order to take into account the within-cluster correlation, to use both within-cluster and between-cluster information, and to take into account any evolution of the intervention effect over time. The mixed logistic model may be used to analyse a cluster randomised trial even when the number of clusters is small, as long as the number of patients per cluster is greater than approximately 30, which is the case in our study. Austin showed that the estimation of the regression coefficient, which quantifies the intervention effect, preserves good properties in terms of bias and coverage probability of the confidence interval, if the number of subjects per cluster is over 30, and even if the number of clusters is as few as five [22]. This analysis will be carried out using the lme4 package of the most recent version of the R software.

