## Methods/design

### Study design

The design of the InPAct protocol is a cluster randomised controlled (CRCT) stepped wedge trial design, which is appropriate for assessing the impact of patient safety interventions [15]. This design involves the sequential rollout of an intervention in the clusters over several time periods. The order in which the clusters will receive the intervention is determined at random, and by the end of the study, all clusters will have received the intervention. Finally, each cluster will successively be situated in a control group and then in an intervention group.

In the InPAct protocol, eight clusters of several GPs were defined. Four steps, one unit (U) of two clusters per step, and five periods (from P1 to P5) of three-month duration were defined. In the first period, the InPAct program will not be implemented. The InPAct program will be rolled out sequentially to the four GP cluster units over the last four time periods (Figure 1). The order in which the clusters will take part in the program is determined at random, allowing the full implementation of the intervention by all participating GPs by the end of the trial [16,17].

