### Sample size

Sample size calculations were carried out using the method implemented by Hussey and Hughes [20]. In our study, the number of clusters was fixed at eight, and the number of time periods was fixed at five. The expected effect of the intervention is an absolute increase of 4.5% of the percentage of hypertensive patients who will report at least one ADE; *i.e.*, an increase from 3% in the group without intervention to 7.5% in the group with intervention. The clustering induces an increase in the variance of the outcome criterion, due to inter-cluster heterogeneity; this increase is quantified by the inter-cluster coefficient of variation. For a given number of patients per cluster, the power of the study was calculated for different coefficients of variation between 0.1 and 0.5, which corresponds to the range of values usually observed. The inclusion of 240 patients per time period (30 patients per cluster) leads to a power greater than 80% regardless of the coefficient of variation (Table 1). The type I error was fixed at 5% for a bilateral test. In the context of the InPAct study, for logistical reasons and to avoid the risks of inter-cluster contamination and clusters with no inclusion, it was preferable to limit the number of GP clusters. With a classic CRCT parallel group design, the number of patients to include would have to be at least 6,000 to maintain a statistical power of 80% with 12 clusters (under 12 clusters it is impossible to reach a statistical power of 80%, regardless of the number of patients), but with our choice of stepped wedge design, the patient number decreases to 1,200 for eight clusters with a statistical power of 80%.

**Table 1 T1:** Statistical power calculated from the coefficient of variation and number of patients per time period

**Cv**	**184 patients per time period**	**208 patients per time period**	**240 patients per time period**
0	0.80	0.85	0.89
0.1	0.80	0.84	0.89
0.2	0.78	0.83	0.87
0.3	0.76	**0**.**81**	0.85
0.4	0.74	0.78	0.83
0.5	0.72	0.76	**0**.**81**

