There are also statistical advantages to choosing a CRCT stepped wedge trial. First of all, GPs are their own controls in both control and intervention groups. This improves comparability in both groups. The CRCT stepped wedge design may also require fewer clusters than a CRCT parallel group design to ensure similar group comparability, in terms of population characteristics. This design therefore increases statistical power compared to parallel group design, because the program effect is estimated not only by between-cluster comparisons but also by within-cluster comparisons. This suggests that the use of a stepped wedge design should decrease patient sample size, compared to a classic CRCT parallel group design [17,20,32]. For the InPAct study, the number of patients to be included (1,200) was calculated to be strongly reduced with a stepped wedge design versus a classic CRCT design, in order to maintain the statistical power of 80% and a cluster number of eight. Additionally, the effects of time can be included in our choice of statistical model, which allows temporal changes in the effectiveness of the program to be considered [16,17,20]. Indeed, the opportunities arising from modelling the effects of time can be illustrated by considering the stepped wedge design as a multiple-arm parallel design, in which the research aims not only to assess intervention effects, but also to determine whether time of intervention affects the effectiveness of the intervention. Such time effects can include seasonal variations both in GP practice and in the reporting, occurrence and progression of ADEs. In general practice, the seasonal variability in the workload of GPs may negatively affect both their availability for providing health information and the effectiveness of the intervention for the patient. The behaviour of both GPs and patients could also be influenced by external factors that are independent of the study, such as a public campaign about a reporting system for ADEs. For the patients, diuretic antihypertensive-associated ADEs such as dehydration may be more serious in summer due to high temperatures. Even if including time as a random effect could be an advantage of the stepped wedge design, Hussey and Hughes have suggested that a relatively complex model might be required to take into account the time effect [20].

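### The tests planned on patient characteristics ignore cluster and period, so the false-positive rate per characteristic exceeds 5% (about 8% to 32% for assumed ICCs of 0.01 to 0.10)

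*Protocol article*

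**What the plan says.** The first paragraph of Statistical analysis is about who was recruited: "The quantitative characteristics of the patients included during the control and intervention periods will be described" by the usual summary statistics. It then sets the tests: "The comparisons between the two groups will be carried out using a" Student t "test or a non-parametric test for the quantitative characteristics and a chi-squared test or a Fisher’s exact test for the qualitative characteristics". Neither a cluster term nor a period term is mentioned.

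The second paragraph treats the effect of the intervention separately: "the analysis of the intervention effect on the main outcome will be carried out using a mixed logistic model" with a random intercept for within-cluster correlation.

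The layout comes from two other sections. Study design: "Four steps, one unit (U) of two clusters per step, and five periods (from P1 to P5) of three-month duration were defined". Sample size: "the number of clusters was fixed at eight, and the number of time periods was fixed at five", and "The inclusion of 240 patients per time period (30 patients per cluster) leads to a power greater than 80% regardless of the coefficient of variation".

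Elsewhere the article recognises both features that the tests leave out. Sample size says that clustering increases the variance of the outcome. The Discussion, on time effects, says: "Such time effects can include seasonal variations both in GP practice and in the reporting, occurrence and progression of ADEs".

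**The concern.** In a stepped wedge the two groups are not two independent samples. Clusters that cross over early supply mostly intervention patients, and clusters that cross over late supply mostly control patients. A stable difference in case mix between clusters therefore leaks into the group comparison. The clusters were formed by geography, shared medical centre or professional ties, across three regions, so such differences are plausible. Control patients also come from earlier calendar periods than intervention patients.

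At stake is how a table of characteristics will be read. GPs recruit the patients, and GPs and patients cannot be blinded (Randomisation section). A reader will naturally look to the comparison of recruited patients for signs of selective recruitment. A small p-value from these tests could come from selection, from between-cluster differences or from calendar time, and the test cannot say which.

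**Working it through.** **Inputs from the article.** 8 clusters, 5 periods, 2 clusters per step, 240 patients per period (240/8 = 30 per cluster and period), two-sided alpha 5%, rates 3% and 7.5%, CV 0.1 to 0.5. **Assumptions.** Equal cluster-period sizes as planned, and the ICC of a patient characteristic, which the article does not give.

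**Step 1: reproduce the plan's own figure.** The Hussey and Hughes variance is I·s²(s² + T·τ²) / [(I·U − W)s² + (U² + I·T·U − T·W − I·V)τ²], with I = 8, T = 5, U = 20, W = 120 and V = 60.
- s² = 0.03 × 0.97/30 = 0.00097. At CV 0.5, τ = 0.5 × 0.03 = 0.015.
- Variance = 8 × 0.00097 × 0.002095 / (40 × 0.00097 + 120 × 0.000225) = 0.000247, so SE = 0.0157.
- z = 0.045/0.0157 = 2.86, and power = 0.817. Table 1 gives 0.81.
- At CV 0 the result is 0.898. Table 1 gives 0.89.

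All 18 cells of Table 1 agree within 0.009. This confirms the layout and shows that the CV is applied to the 3% rate.

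**Step 2: how clusters enter the naive difference.** There are 20 control and 20 intervention cluster-periods, so 600 v 600 patients. A cluster's weight is its share of the intervention group minus its share of the control group.

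| Unit (2 clusters) | Control : intervention periods | Weight per cluster |
|---|---|---|
| Crosses at P2 | 1 : 4 | 120/600 − 30/600 = +0.15 |
| Crosses at P3 | 2 : 3 | 90/600 − 60/600 = +0.05 |
| Crosses at P4 | 3 : 2 | −0.05 |
| Crosses at P5 | 4 : 1 | −0.15 |

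The sum of squared weights is 4 × 0.0225 + 4 × 0.0025 = 0.10. With total variance 1, the true variance of the difference is 0.10 × ICC + (1 − ICC) × 2/600. The naive test uses 2/600. The ratio is 30 × ICC + 1 − ICC = 1 + 29 × ICC.

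**Step 3: false-positive rate per characteristic.** True alpha = 2 × [1 − Φ(1.96/√(1 + 29 × ICC))]. The last two columns are simulations with 20,000 trials per ICC.

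| Assumed ICC | Variance ratio | Closed form | Simulated t test | Simulated chi-squared (prevalence 50% / 10%) |
|---|---|---|---|---|
| 0 | 1.00 | 5.0% | 5.1% | 5.5% / 4.9% |
| 0.0077 | 1.22 | 7.6% | 7.6% | 8.0% / 8.0% |
| 0.01 | 1.29 | 8.4% | 8.3% | 8.5% / 8.3% |
| 0.02 | 1.58 | 11.9% | 11.7% | 12.3% / 12.3% |
| 0.05 | 2.45 | 21.1% | 21.6% | 21.7% / 20.6% |
| 0.10 | 3.90 | 32.1% | 32.1% | 33.1% / 30.9% |

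The non-parametric and Fisher tests were not simulated; they make the same independence assumption.

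**Step 4: what the article's own CV implies.** ICC = CV² × p/(1 − p). At p = 3%, CV 0.1 gives 0.0003 and CV 0.5 gives 0.0077, so the rate is 5.1% to 7.6%. The same CVs on a characteristic with an assumed prevalence of 30% give ICCs of 0.004 to 0.107 and rates of 6.5% to 33%.

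**Step 5: calendar time.** Mean period of control patients: (8×1 + 6×2 + 4×3 + 2×4)/20 = 2.0. Mean period of intervention patients: (2×2 + 4×3 + 6×4 + 8×5)/20 = 4.0. A linear drift of d per period in a characteristic therefore separates the groups by 2d.

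**Step 6: does adjustment repair it?** Cluster-period means were analysed with cluster and period effects (both fixed, 5,000 runs). The rate was 5.0%, 4.5% and 5.0% at ICC 0.01, 0.05 and 0.10. A random-intercept version was not simulated.

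**The case against.** The strongest reply is that this is a descriptive paragraph. Nothing in the article depends on these p-values: no covariate is selected by them and no decision follows. That stands, and it limits the severity. It does not make the p-values correct, and the tests are named outright rather than left to a fuller document.

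The size is also open to challenge. The upper rates need ICCs that the article does not state, and its only heterogeneity figure gives 5% to 8%. That also stands. But that CV describes a rare outcome, and Step 4 shows that the same CV means a much larger ICC for a common characteristic.

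Four stronger readings are tempting, and the article does not support them.
- *The trial's result is compromised.* It is not: the effect on the main outcome is tested with the mixed logistic model.
- *Secondary outcomes will be tested this way.* The sentence ties these tests to patient characteristics. The article does not say how secondary outcomes are analysed, and a fuller plan may.
- *A trend produces false positives at very high rates.* With an assumed drift of 0.05 or 0.10 SD per period, the groups truly differ by 0.10 or 0.20 SD. Against SE √(2/600) = 0.058, the test rejects in about 41% or 93% of cases. That is detection of a real calendar difference, and the difficulty lies in its interpretation. A purely seasonal pattern would matter less than a steady trend: P1 and P5 fall in the same season and together supply 40% of each group, which leaves only P2 (30% of controls v 10% of intervention patients) and P4 (10% v 30%) unbalanced.
- *This comparison is the trial's designated check on recruitment.* The article never calls it that; it is a use that readers are likely to make of it.

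**Conclusion.** The point holds for the comparison of patient characteristics, at minor to moderate severity. The named tests are not valid for clustered patients: in the planned layout their false-positive rate exceeds 5% for any positive ICC. How far it exceeds 5% depends on ICCs that have to be assumed, so the 8% to 32% range is conditional on ICCs of 0.01 to 0.10 and is not an estimate for this trial. It applies to each characteristic tested; it is not the share of trials that go wrong. The article's own primary-outcome CV sets a lower reference of about 5% to 8%. Separately, and whatever the ICC, the two-period gap between the groups means that these tests cannot separate a calendar trend in case mix from selective recruitment.

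**What to change.** In the first paragraph of Statistical analysis, delete the sentence on t, non-parametric, chi-squared and Fisher tests. State instead that characteristics will be described by group and by period, without p-values.

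If a test of balance is wanted, specify for each characteristic a model with a cluster random intercept, period as a categorical factor and the group indicator. It should be read with the small number of clusters (eight) in mind.

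The change is to analysis wording only. It needs no new data and leaves recruitment, conduct and the primary analysis as they are. The Trial status section says that data cleaning and analysis had not begun at submission, so at that point it could be made before any results were seen.

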### 2. General practitioner training

GP investigators will receive booklets and will participate in a web seminar explaining the kind of oral information to provide when the booklet is given to the patient. As determined by the pilot study, physicians are encouraged to give the booklet to the patient and to first present the principal value of the booklet for the patient, that is, the reporting of ADEs for increased patient safety [18]. In order to increase physician-patient interaction and communication, physicians are encouraged to first ask several questions to evaluate patient knowledge of the benefits and risks of the antihypertensive drug prescription, and to then give some complementary information. GPs are asked to present the care plan to the patient and to explain the antihypertensive drug prescription. Also, GPs are incited to explain the lab tests planned for the patient follow-up and to present to the patient the open text box for patient questions in the care plan. Once the booklet has been presented to the patient in this manner, GPs must again remind the patient of the main value of the booklet and describe the content of the ADE report form. Our hypothesis is that the InPAct booklet should facilitate the interaction between GPs, who are primary healthcare professionals, and their patients, leading to improve ADE reporting by patients.

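### The protocol says its random-intercept model allows for a changing intervention effect, but one coefficient cannot do that, and if the effect changes, that coefficient mostly reflects the first quarters after training

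*Protocol article*

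**What the plan says.** **Layout.** Under Study design: "Four steps, one unit (U) of two clusters per step, and five periods (from P1 to P5) of three-month duration were defined". In addition, "In the first period, the InPAct program will not be implemented" and "The InPAct program will be rolled out sequentially to the four GP cluster units over the last four time periods". The first unit is therefore observed for four quarters after crossover and the last for one.

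**Intervention.** Under General practitioner training, GPs "will participate in a web seminar explaining the kind of oral information to provide when the booklet is given to the patient". What the patient receives depends partly on a skill taught to the GP.

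**Analysis.** The Statistical analysis section names a mixed logistic model with a random intercept, following Hussey and Hughes. Among its reasons for this model it lists allowing for change in the intervention effect over time. The abstract adds that the model covers cluster and time effects. The effect measure appears as "the regression coefficient, which quantifies the intervention effect", in a sentence reporting a cited simulation study that the protocol uses to justify its own model.

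**Discussion.** The section on the advantages of the stepped wedge design says that time effects in the model let changes in the program's effectiveness be examined. No term for time since crossover, no treatment-by-time term and no random treatment effect is named anywhere.

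**The concern.** Period effects and a changing intervention effect are different things. Period effects absorb movements in the reporting rate that all clusters share, such as season or a public campaign. They do not let the difference between intervention and control grow or shrink as GPs gain practice or lose interest. A model with one intervention coefficient assumes that this difference is constant, so the plan credits its model with a property the model lacks.

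If the effect is not constant, the coefficient still gives a number, but the layout decides what it averages. The Discussion foresees using the result to support implementation in other regions. A front-loaded figure would overstate a program that fades and understate one that needs practice.

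**Working it through.** **Inputs.** From Study design and Sample size: 8 clusters, 5 periods, two clusters crossing over at each of P2 to P5, and 30 patients per cluster-period ("The inclusion of 240 patients per time period (30 patients per cluster) leads to a power greater than 80"%). The rates are "an increase from 3% in the group without intervention to 7.5% in the group with intervention". Table 1 covers Cv 0 to 0.5; the abstract gives 0.5 as the design value.

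**Step 1: reproduce Table 1.** Take σ² = 0.03 × 0.97 / 30 = 0.00097 and τ = Cv × 0.03. The Hussey and Hughes variance is

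Var = Iσ²(σ² + Tτ²) / [(IU − W)σ² + (U² + ITU − TW − IV)τ²],

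with I = 8, T = 5, U = 20 intervention cells, W = 0 + 4 + 16 + 36 + 64 = 120 and V = 2 × (16 + 9 + 4 + 1) = 60. The brackets are 160 − 120 = 40 and 400 + 800 − 600 − 480 = 120.

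At Cv 0.5, τ² = 0.000225:
- Numerator: 8 × 0.00097 × 0.002095 = 0.00001626
- Denominator: 40 × 0.00097 + 120 × 0.000225 = 0.0658
- Standard error: √0.000247 = 0.0157, that is 1.57 points
- Power: Φ(0.045/0.0157 − 1.96) = 0.817, against 0.81 in Table 1

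All 18 cells of Table 1 agree within 0.01, so this is the plan's own planning model.

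**Step 2: weights of the single coefficient.** With fixed period effects and a random cluster intercept, the generalised least squares coefficient weights each cell in proportion to

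(X − period mean of X) − φ × (cluster's intervention periods − 2.5), where φ = τ²/(σ² + Tτ²).

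Units have 4, 3, 2 and 1 intervention periods, so the deviations from 2.5 are 1.5, 0.5, −0.5 and −1.5. Period means of X in P2 to P5 are 0.25, 0.50, 0.75 and 1. Summing over the intervention cells by quarter since crossover (two clusters per unit):
- Quarter 1: 2 × (0.75 + 0.50 + 0.25 + 0) − 2φ × 0 = 3
- Quarter 2: 2 × (0.50 + 0.25 + 0) − 2φ × 1.5 = 1.5 − 3φ
- Quarter 3: 2 × (0.25 + 0) − 2φ × 2 = 0.5 − 4φ
- Quarter 4: 0 − 2φ × 1.5 = −3φ
- Total: 5 − 10φ

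Dividing each by the total:

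| Cv | φ | Q1 | Q2 | Q3 | Q4 |
|---|---|---|---|---|---|
| 0 | 0 | 0.60 | 0.30 | 0.10 | 0.00 |
| 0.1 | 0.0089 | 0.61 | 0.30 | 0.10 | −0.01 |
| 0.3 | 0.0589 | 0.68 | 0.30 | 0.06 | −0.04 |
| 0.5 | 0.1074 | 0.76 | 0.30 | 0.02 | −0.08 |

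Planned intervention cells by quarter are 8, 6, 4 and 2 of 20, or 240, 180, 120 and 60 patients. The patient shares are therefore 0.40, 0.30, 0.20 and 0.10. No row of the table matches them.

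**Step 3: what this does to an estimate (assumed patterns, Cv 0.5).**
- Fading 6, 4.5, 3, 1.5 points: the coefficient targets 5.9; the patient mean is 4.5.
- Building 1.5, 3, 4.5, 6 points: it targets 1.6; the patient mean is 3.0.
- Mild fading 5, 4.5, 4, 3.5 points: it targets 4.96; the patient mean is 4.5.
- Constant 4.5 points: it targets 4.5.

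**Step 4: logistic scale.** A linearised check at 3% and 7.5% gives 0.64/0.28/0.08/0.00 with no between-cluster variation. With an assumed random-intercept standard deviation of 0.5 on the logit scale it gives 0.94/0.28/−0.07/−0.15. The numbers differ from the linear ones, but the pattern is the same.

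**The case against.** **The article does not list the model's terms, and the analysis plan is not shown.** The quoted words come from a sentence about a cited study, and the exact coding could well be in an analysis plan. This stands as far as missing detail goes. It does not answer the point, which is that the article names a random intercept as the means of handling a changing effect, and a random intercept does not do that.

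**The exact weights are conditional.** They belong to a linear model with fixed period effects and equal cells, and the steepest set is at the top of the Cv range. A reader might take 0.76/0.30/0.02/−0.08 as the weights of the primary logistic analysis; the documents do not support that. At Cv 0.1 the negative weight almost vanishes. The Discussion also mentions time as a random effect. With a very small period variance that would move the Cv 0.5 weights to about 0.45/0.30/0.18/0.08, close to the patient shares.

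**The harm depends on how much the effect changes.** Each patient is newly enrolled and followed for three months, so only GP behaviour can drift. No passage supports a fourfold change. Under the mild pattern the gap is 4.96 − 4.5 = 0.46 points, about 0.3 of the 1.57-point standard error. This stands.

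**Loss of power.** A reader might infer that the trial would probably miss a program that builds up. In simulated logistic fits of the building pattern, 15% of trials were significant. That pattern also averages only 3.0 points, and a constant 3.0-point effect has power of only Φ(0.030/0.0157 − 1.96), about 48%, on the plan's variance. Part of the shortfall is therefore the smaller assumed effect, and the 15% should not be put down to the weighting alone.

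**Conclusion.** The point holds as a mismatch between a stated property and the named model. At every Cv in Table 1, quarters 1 and 2 carry at least 0.90 of the weight but hold 0.70 of the planned intervention patients. At Cv 0.5, quarters 3 and 4 hold 0.30 of the patients and get a net weight of about −0.06. These figures assume fixed period effects, equal cluster-periods and the linear planning variance.

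A reader might go further and conclude that the primary test is invalid or that the estimate is biased whatever happens. Neither follows. With a constant effect, the coefficient is unbiased for it in this respect. With no effect at any time since training, the test is unaffected. What is at risk is the reading of the effect size, and only if the effect changes with time since training. This is worth correcting, but it does not undermine the design.

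**What to change.** 1. Keep the single-coefficient model as the primary test and estimate.
2. Correct the sentence in Statistical analysis so that it no longer says this model handles a changing effect. State that the coefficient mainly reflects the first quarters after training if the effect is not constant.
3. Pre-specify one supporting model with the same random intercept, fixed period effects and intervention terms for quarter 1, quarter 2, and quarters 3 and 4 pooled since the cluster's crossover. Pooling is needed because quarter 4 has only 60 planned patients. At an assumed rate of 4.5% that is 2.7 expected events, and the chance of none is 0.955^60, about 6%, in which case a separate logistic term has no finite estimate.
4. Always report the patient-weighted average of these terms (planned shares 0.40/0.30/0.30) with its interval beside the primary estimate. Do not make the headline figure depend on how far the two differ.

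**Cost.** One extra model on data already held, and some wording. The average is less precise. With four separate quarter terms on the plan's variance, its standard error is about 1.77 against 1.57 points at Cv 0.5, and 1.47 against 1.41 at Cv 0.1. Pooling assumes one effect for quarters 3 and 4, so a difference between them would not be seen. The planned shares follow from the rollout schedule, so the average describes this trial's intervention patients and is not a long-run effect.
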